**Figure 1. SPIRIT Figure - Schedule of enrolment, interventions, and assessments**

| TIMEPOINT**                                                    | STUDY PERIOD |            |                 |     |     |     |      |           |
|----------------------------------------------------------------|--------------|------------|-----------------|-----|-----|-----|------|-----------|
|                                                                | Enrolment    | Allocation | Post-allocation |     |     |     |      | Close-out |
|                                                                | -1 w         | 0 w        | 2 w             | 4 w | 6 w | 8 w | 10 w | 12 w      |
| ENROLMENT:                                              |              |            |                 |     |     |     |      |           |
| Eligibility screen                                             | X            |            |                 |     |     |     |      |           |
| Informed consent                                               | X            |            |                 |     |     |     |      |           |
| Randomized by independent person                               | X            |            |                 |     |     |     |      |           |
| Allocation                                                     |              | X          |                 |     |     |     |      |           |
| INTERVENTIONS:                                          |              |            |                 |     |     |     |      |           |
| Intervention group:
Smart Speaker
EchoDot 3rd Gen |              | ←          | →               | →   | →   | →   | →    | →         |
| Control group:
usual care                            |              | ←          | →               | →   | →   | →   | →    | →         |
| Follow up phone calls                                   |              |            | X               | X   | X   | X   | X    |           |
| ASSESSMENTS:                                            |              |            |                 |     |     |     |      |           |
| Demographic information and baseline data               | X            |            |                 |     |     |     |      |           |
| SRQ-20 (primary outcome)                                | X            |            |                 |     |     |     |      | X         |
| SF-36                                                   | X            |            |                 |     |     |     |      | X         |
| SCI-R                                                   | X            |            |                 |     |     |     |      | X         |
| PSS                                                     | X            |            |                 |     |     |     |      | X         |
| Blood pressure                                          | X            |            |                 |     |     |     |      | X         |
| Glycated hemoglobin (HbA1c)                             | X            |            |                 |     |     |     |      | X         |
| Lipid profile                                           | X            |            |                 |     |     |     |      | X         |

**Table 4: Logistic and assessments of each visit during the study period**

| Visit                                      | Baseline Evaluation
(week -1) | Installation of the
device* (week 0) | Final Evaluation
(week 12) |
|--------------------------------------------|----------------------------------|-----------------------------------------|-------------------------------|
| Predetermined duration of visit (minutes)  | 120                              | 15                                      | 60                            |
| Protocol assessment time windows (days)    | NA                               | ±7                                      | ±7                            |
| Identification data                        | X                                |                                         |                               |
| Clinical interview and baseline evaluation | X                                |                                         |                               |
| Clinical evaluation                        | X                                |                                         | X                             |
| Laboratory evaluation                      | X                                |                                         | X                             |
| Medication use                             | X                                |                                         | X                             |
| Installation of device                     |                                  | X                                       |                               |

\*This applies only to participants from the intervention group. Participants in the control group will receive an additional phone call in week 0 to ensure equivalency. NA refers to not applied.

**Table 5. Logistic of phone calls during the study period**

| Phone call    | Week of study |
|---------------|---------------|
| Phone call 0* | Week 0        |
| Phone call 1  | Week 2        |
| Phone call 2  | Week 4        |
| Phone call 3  | Week 6        |
| Phone call 4  | Week 8        |
| Phone call 5  | Week 10       |

\*Only for participants from the control group. Equivalent to installation of the device.

## 9.1. Data collected

**Identification data:** Full name, medical record number, phone number, address, and email address.

**Clinical interview and baseline evaluation:** Sociodemographic information, comorbidities and personal medical history, daily schedule, mini-mental state examination (MMSE) score,

up and go test, sit-to-stand test, usual gait speed test, height, hip and calf circumference, Katz activities of daily living index score, and Lawton instrumental activities of daily living scale

**Clinical evaluation:** Blood pressure (three repeated measures), handgrip strength (three repeated measures in the non-dominant arm), body weight, and score on the Brazilian version of the following:

- SRQ-20
- SF-36
- SCI-R
- PSS

**Laboratory evaluation:** Glycated hemoglobin, fasting plasma glucose, total cholesterol, HDL-c, LDL-c, triglycerides, serum creatinine, and albumin and creatinine (urine sample)

**Medication use:** Name and daily dosage of medications, vitamins and nutritional supplements, if in use

**Installation of the device:** During installation of the device no data is collected.

**Follow-up phone calls:** General information about well-being and adverse events

## **10. Missing appointments, early withdrawal, and loss of follow-up of participants**

In order to reduce the number of missed appointments, a standardized message will be sent 1 day prior to the scheduled appointment to remember and confirm attendance. If a participant misses an appointment, they will be contacted by phone call to reschedule. To minimize dropouts and missing data, all eligible participants will be informed of the importance of attending follow-up visits during the baseline visit and in every follow-up phone call. If a participant requests early withdrawal from the study, they will be asked to attend to final evaluation to collect endpoint measurements.

Before considering a participant as unresponsive and proceeding to exclude them from the study due to a lack of contact we will conduct 9 phone call attempts (three phone calls at three different moments), in addition to attempts to contact them through WhatsApp messages. Also, three Smart Speaker EchoDot 3rd Gen (Amazon Echo®) devices will be randomly awarded as incentives among participants who successfully complete the study. This strategy aims to encourage participants to provide complete data, thus improving the overall data quality of the study.

## 11. Sample size

Sample size calculations were performed using the Statistics and Sample Size Pro software (6). With an alpha level of 0.05, a power of 90%, and an effect size of 0.68 (Cohen's d), it was estimated that 94 subjects (47 per group) would be required to assess mean differences in the primary outcome. Assuming a 20% dropout rate, we plan to include 112 subjects (56 per group) in the study. The effect size of 0.68 was based on the randomized controlled trial published by Fulmer R et al. (7), which evaluated the efficacy of using psychological artificial intelligence software to reduce self-identified symptoms of depression and anxiety.

## 12. Statistical analysis plan

This document serves as the formal statistical analysis plan (SAP) (version 1.0) for the trial. The detailed SAP was elaborated following the guidance published by Gamble et al. (2017)(8).

### 12.1 Descriptive statistics and baseline data

A consolidated standards of reporting trials (CONSORT) style flow diagram will present the number of patients screened and all reasons for exclusions prior to randomization (9). Demographic and socioeconomic information (including age, sex, race, socioeconomic status, and educational level), baseline clinical characteristics (such as body mass index [BMI], glycated hemoglobin, systolic and diastolic blood pressure, insulin usage, smoking status, alcohol consumption, comorbidities, performance on up and go, gait speed, and sit and stand tests, and others), as well as other variables, will be described by arm and overall. Categorical variables will be described as frequency (percentage). Continuous variables will be described as mean  $\pm$  standard deviation (SD) or median and interquartile range. Hypothesis testing for differences in baseline characteristics between the intervention and control arms will not be performed, in accordance with the CONSORT guideline.

### 12.2. Primary and secondary outcome analysis

All analysis will be performed after the end of the trial and no interim analysis will be performed. The analysis of all study outcomes will be carried out using analysis of covariance (ANCOVA), as all the outcomes are quantitative. This approach will allow a comparison of means between groups, while also considering potential variations in covariates. As we will compare the means at the end of the study, rather than deltas

(differences from baseline), the model will include baseline data of the outcome variable as a covariate. This adjustment allows us to account for the initial variation in scores among the groups before assessing any potential intervention effects.

All analysis will be performed using the intention-to-treat approach, including all subjects who were randomized. Per protocol analysis will only be performed as a sensitivity analysis, as described in the section 12.3. Normality tests for outcome data will not be performed. Instead, we will conduct visual histogram and QQ plot analyses. If distributional assumptions are in doubt, we will perform a logarithmic transformation of the data before analysis.

### 12.3. Missing data

The imputation of missing data will be handled following the European Medicines Agency Guideline on Missing Data in Confirmatory Clinical Trials (10). The overall rate of missing data at week 12 is expected to be no more than 20% and the frequency and reasons for missing data are expected to be missing at random (MAR). However, the possibility of missing not at random (MNAR) cannot be excluded, as we believe that three factors may influence the missing data:

1. Participants less familiar with technology may have a higher tendency to dropout and might experience reduced benefits due to a higher likelihood of non-adherence to the intervention.

2. Participants from the usual care group may have a higher tendency to discontinue participation due to not receiving the device as they expected.

3. Older participants, who are less likely to experience intervention-related benefits, may be more likely to miss the final evaluation due to potential mobility challenges and a greater reliance on caregiver assistance to attend the consultation.

Therefore, to explore the potential impact of missing data in different scenarios, promoting a better understanding of how different methods of handling missing data impact our results considering the challenge of handling missing data within the possibility of MNAR assumption, three distinct imputation strategies will be employed to assess the impact of missing data on our results:

1. *Multiple imputation with baseline data correction*: we will perform multiple imputation of missing data correcting for the baseline data. This correction aims to mitigate potential bias that could be introduced by missing data imputation using multiple imputation under a possible MNAR assumption.

2. *Baseline Observation Carried Forward (BOCF)*: given our anticipation and belief that both control and intervention subjects are likely to exhibit improvement regarding the baseline parameters, we will adopt the BOCF technique as a sensitivity analysis. By carrying forward the baseline observation, our analysis will be conducted within a more conservative scenario that tends toward the null hypothesis, reducing the probability of type 1 error related to missing data imputation.

3. *Exclusion of participants with missing data*: furthermore, we will conduct a sensitivity analysis considering only the trial completers. As this analysis has the potential to introduce selection bias, the results will be treated as hypothesis generation as subjects with missing data may differ in certain aspects from those without missing data.

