#### 12.7. Confidence intervals, p-value and reporting conventions

Statistical significance level for primary outcome will be at the 0.05 level ( $\alpha = 0.05$ ). 95% confidence intervals for all study outcomes, as well as for all subgroup and sensitivity

analysis will be reported. P-value values  $\geq 0.001$  will be reported to 3 decimal places; values  $< 0.001$  will be reported as “ $< 0.001$ ”. Mean and SD values will be reported using one decimal place greater than the original data. Median and quantiles will use the same number of decimal places as the original data. Subjects who attend to baseline evaluation and final evaluation visits will be considered trial completers.

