### 19. List of abbreviations

|         |                                                                    |
|---------|--------------------------------------------------------------------|
| SPIRIT  | Standard Protocol Items: Recommendations for Interventional Trials |
| HSL     | Hospital São Lucas                                                 |
| PUCRS   | Pontifícia Universidade Católica do Rio Grande do Sul              |
| SRQ-20  | Self Reporting Questionnaire 20                                    |
| SCI-R   | Self-Care Inventory Revised                                        |
| SF-36   | 36-Item Short Form Health Survey                                   |
| PSS     | Perceived Stress Scale                                             |
| HDL-c   | high-density lipoprotein cholesterol                               |
| LDL-c   | low-density lipoprotein cholesterol                                |
| SAP     | Statistical analysis plan                                          |
| CONSORT | Consolidated Standards of Reporting Trials                         |

|       |                                                                         |
|-------|-------------------------------------------------------------------------|
| BMI   | Body Mass Index                                                         |
| SD    | Standard Deviation                                                      |
| MAR   | Missing at Random                                                       |
| MNAR  | Missing Not at Random                                                   |
| BOCF  | Best Observation Carried Forward                                        |
| ID    | Identification number                                                   |
| CNPq  | Brazilian National Council for Scientific and Technological Development |
| CAPES | Coordination for the Improvement of Higher Education Personnel          |
| IRB   | Institutional review board                                              |

547

548

549

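### The claim that BOCF is conservative and lowers type I error does not follow: with no true effect it favours whichever arm has less dropout

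*Combined protocol and SAP*

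**What the plan says.** Section 12.3 expects at most 20% of week-12 data to be missing overall. It works mainly with missing at random but accepts that missing not at random cannot be ruled out. The second of its three reasons is that "Participants from the usual care group may have a higher tendency to discontinue participation due to not receiving the device as they expected".

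It then lists three strategies: multiple imputation with a baseline correction, BOCF, and an analysis of completers. The argument for BOCF starts from the belief that "both control and intervention subjects are likely to exhibit improvement regarding the baseline parameters" and concludes that "our analysis will be conducted within a more conservative scenario that tends toward the null hypothesis, reducing the probability of type 1 error". BOCF is expressly a sensitivity analysis. Multiple imputation comes first in the list but is not explicitly named as primary.

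Under section 12.2 all outcomes are analysed by ANCOVA of the week-12 value with baseline as covariate. Section 19 expands the abbreviation as "Best Observation Carried Forward", whereas section 12.3 says Baseline.

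**The concern.** BOCF assigns zero change to everyone without a final value. If both arms are improving, each arm loses improvement in proportion to its own dropout, and the two losses cancel only when dropout is equal. So the premise used to call BOCF conservative, improvement in both arms, is what allows it to create a difference. If the usual-care arm loses more people, that difference favours the device. The trial is open after baseline (section 5.3), so controls know that they did not get one.

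Section 12.3 already treats the completer analysis as hypothesis-generating. BOCF is therefore the only strategy presented as guarding against a false positive. If multiple imputation and BOCF both showed a benefit, a reader would be told that a conservative check agrees, although that check may itself lean toward the device.

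**Working it through.** **Inputs from the documents.** Significance: "Statistical significance level for primary outcome will be at the 0.05 level" (section 12.7), taken as two-sided. Sample size (section 11): effect size 0.68, power 90%, "94 subjects (47 per group) would be required to assess mean differences in the primary outcome", and "Assuming a 20% dropout rate, we plan to include 112 subjects (56 per group) in the study". Overall missingness at most 20%, improvement in both arms, possibly more dropout in controls (section 12.3). SRQ-20 runs from 0 to 20, lower being better (section 7.1).

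**Inputs not in the documents, so assumed.** Dropout by arm, size of improvement, SD of SRQ-20, and the baseline to week-12 correlation.

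**The plan's own figure.** No type I error is stated for BOCF. The sample size does reproduce: a two-sided t-test with d = 0.68 needs 47 per arm (power 90.4%). The normal approximation gives 46, and a one-sided test would need only 38. The randomised number matches 47 × 1.2 = 56.4, taken as 56. I use 56 per arm.

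**Formula.** Let δ be the mean improvement in controls, τ the extra improvement from the device, and dC and dI the control and device dropout. Dropouts are taken to be like others in their arm. After BOCF:

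- control improvement = (1 − dC)δ
- device improvement = (1 − dI)(δ + τ)
- estimated effect = (1 − dI)τ + (dC − dI)δ
- bias = (dC − dI)δ − dI·τ

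With no true effect (τ = 0) the bias is (dC − dI)δ. At 30/10 with 2 points it is 0.20 × 2 = 0.40 points toward the device.

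**Simulated type I error, no true effect.** BOCF then ANCOVA, 56 per arm, SD 4, correlation 0.6, overall dropout 20%, dropout random within arm. Ranges are over separate runs.

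| Control/device dropout | Improvement in both arms | Spurious effect for device | Type I error |
|---|---|---|---|
| 20/20 | 2 points | 0 | 4.9–5.7% |
| 25/15 | 2 points | 0.10 × 2 = 0.20 | 6.6% |
| 25/15 | 3 points | 0.10 × 3 = 0.30 | 7.5% |
| 30/10 | 1 point | 0.20 × 1 = 0.20 | 6.6% |
| 30/10 | 2 points | 0.20 × 2 = 0.40 | 10.2–10.6% |
| 30/10 | 3 points | 0.20 × 3 = 0.60 | 16.8–17.3% |
| 35/5 | 2 points | 0.30 × 2 = 0.60 | 18.6–19.2% |

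At 30/10 with 2 points, 9.8 of the 10.2 percentage points favour the device.

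**Check on a standardised scale** (20,000 runs per scenario, correlations 0.5 and 0.7, improvement 0.25 to 1.0 SD):

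- Equal dropout: 4.8–5.4%.
- 25/15: 5.4–10.8%.
- 30/10: 6.3–28.6%.
- 15/25, device dropout higher: 5.4–10.5%, with the excess favouring control.
- Completer ANCOVA: 4.6–5.4% throughout. This is expected, because dropout was random within arm, and it does not show that the completer analysis is safe in general.

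**With a true effect of 0.68 SD.**

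- Equal 20% dropout: 0.80 × 0.68 = 0.54 SD, attenuated.
- 25/15, δ = 0.25 SD: 0.85 × 0.68 + 0.10 × 0.25 = 0.60 SD, still attenuated.
- 30/10, δ = 1.0 SD: 0.90 × 0.68 + 0.20 × 1.0 = 0.81 SD, exaggerated.

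**The case against.** The strongest reply is that little depends on this. BOCF is a sensitivity analysis, and no rule ties the trial's conclusion to it. A reader might infer that the trial's own type I error is inflated; the documents do not support that.

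Nor is differential dropout certain. The plan says only that controls may leave more often. Its other two factors, unfamiliarity with technology and older age, are not tied to the control arm, and the first could raise dropout in the device arm. Section 10 raffles devices among completers and asks early withdrawers to attend the final evaluation; both could narrow the gap. With a 25/15 split the inflation is modest. Eligibility requires no baseline distress and SRQ-20 has a floor at zero, so room for a 2- or 3-point improvement is not established. If dropouts would have improved little, the bias shrinks. These points stand and limit the size.

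Three stronger readings are also tempting and should be resisted:

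- **That BOCF always leans toward the device.** It does not. It can attenuate a true effect even when control dropout is higher, and with no true effect and higher device dropout it leans toward control.
- **That BOCF is the planned analysis most likely to produce a false benefit.** This is not shown. Multiple imputation was not simulated, and neither was outcome-dependent dropout.
- **That a best-observation method is planned.** Section 12.3 plainly describes the baseline value, so the entry in section 19 is a clerical slip.

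None of this rescues the sentence in the SAP. A type I error claim concerns the case of no effect, and there BOCF gives no reduction at equal dropout and an increase at unequal dropout when both arms improve.

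**Conclusion.** The point holds as a defect in the stated rationale. Attenuation of a true effect, which BOCF can produce, is a loss of power; it is not protection against a false positive. Under the SD 4 assumptions, type I error is about 5% with equal dropout, about 5–8% at 25/15 control/device (1 to 3 points' improvement), 6–17% at 30/10 (1 to 3 points) and about 19% at 35/5 (2 points). The direction rests on three conditions: improvement in both arms, higher control dropout, and dropouts who would have improved like others in their arm. The first is expected in section 12.3, the second is named there as possible, and the third is my assumption. The sizes rest on figures that the plan does not give.

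This should be fixed, but it is not critical, because the main analysis is not directly affected. It matters because the plan has no sensitivity analysis that varies the missing-not-at-random assumption by arm.

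**What to change.** Before group codes are disclosed:

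1. Delete from section 12.3 the statements that BOCF is conservative, tends toward the null and reduces type I error.
2. Report dropout by arm beside any BOCF result, so that the direction of its bias can be judged.
3. Replace or supplement BOCF with delta-adjusted multiple imputation (tipping point) for SRQ-20. Shift the imputed values separately in each coded arm over a two-way grid, for example 0 to 4 points worse, and report where the primary conclusion changes. Because the grid treats the coded arms symmetrically, analyst blinding under section 5.3 is kept.
4. Correct Best to Baseline in section 19.

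Items 1, 2 and 4 cure the error. Item 3 supplies the check that BOCF was meant to provide. The cost is some SAP wording, a short program and one more sensitivity table; no new data are needed.
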